### Knowledge Gaps

Although foods purchased and eaten away from home can impact nutritional status [13,21], the most recent Australian National Nutrition and Physical Activity Survey did not collect data on the source of the food and beverages consumed [22]. Limited research has focused on specific food types that may or may not have been sourced outside the home [23] or on determinants of fast food intake [8,24]. Only one Australian study has been conducted on the consumption of foods purchased outside of home and how this affects the total diet [25]. However, that analysis was conducted using data collected more than 20 years ago, and as Australians’ expenditure on fast foods and eating out has been increasing [9], as have the rates of overweight and obesity, it is timely to revisit the role of eating out on diet quality and risk factors for chronic disease. The exact quantities, type, and frequency of consumption of food prepared outside home by young adults and the impact this has on their energy, macronutrient, and micronutrient intakes is currently unknown. To address these gaps in knowledge, the proposed project will collect data on the frequency, type, amount, and place of purchase of foods prepared away from home, together with sociodemographic data in a population sample of 18- to 30-year-old Australians.

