### Population Sampling

Purposive sampling will be conducted to ensure quotas for different demographics are captured. Individuals are eligible to enroll in the study if they: (1) are aged 18 to 30 years; (2) reside in NSW; (3) own or have access to a smartphone; (4) can read, write, and understand English; and (5) consume at least one meal, snack, or drink purchased outside the home per week. As the data will be collected using a smartphone app in English, it is important that the participants have access to a smartphone and are proficient in written English. The study is specifically focused on foods eaten away from home, so it is important that participants eat out at least once per week. Participants will be excluded if they do not meet the aforementioned criteria, are not able to commit to 3 consecutive days of data collection, are pregnant and/or breastfeeding, or have ever been diagnosed or treated for an eating disorder. Pregnant women and breastfeeding mothers will be excluded as their nutritional requirements, and potentially eating habits, change during this time. Those who have been diagnosed or treated for an eating disorder will be excluded because of ethical reasons.

A total of 1008 participants will be recruited to the study, across a range of geographic areas and demographic factors, which provides a margin of error of ±3% on all estimates of proportions (with 95% CI). An even spread of males and females will be recruited. The sample will be constituted to ensure an even distribution of participants in the older age bracket (25 to 30 years) and the younger age bracket (18 to 24 years); from metropolitan and regional areas (as defined by the Accessibility/Remoteness Index of Australia (ARIA+) [29] based on the postcode of the area the participant resides, with major cities considered “metropolitan” and all other areas “regional”); and from lower and higher SES areas (as defined by the Index of Relative Socio-economic Advantage and Disadvantage (IRSAD) [30] based on the postcode of the area where the participant resides) with “low” SES, including deciles 1-5 and “high” SES deciles 6-10). The sampling diagram is shown in Multimedia Appendix 1.

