### Recruitment

Participants will be recruited using a range of methods. The study is being conducted in partnership with Cancer Council NSW, a large nongovernment organization that leads a variety of public health research, health promotion, and fundraising activities. Cancer Council NSW has both a head office and a regional structure that allows recruitment across a diverse selection of ARIA+ and IRSAD codes across the state.

One recruitment method will be to recruit through Relay For Life, a community-driven fundraising event, where teams walk or run laps of a running track for 12 to 24 hours [31]. The Relay For Life events are held in both urban and regional centers, and attract approximately 134,000 participants from a broad cross-section of community in Australia annually [32]. During the event, there are other activities and information stands for participants and spectators, where participants will be recruited.

Additional recruitment will be conducted through electronic newsletters, noticeboards, and social media via Cancer Council NSW and The University of Sydney organizational channels. Snowball sampling will also be utilized, with participants encouraged to forward the study details to their own contacts. The recruitment and participation process is summarized in Figure 1.

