### Statistical Analysis

#### Mean Intake of Energy and Nutrients

Data collected from the EaT app will be used to determine mean, median, and 95% CI of daily intakes of energy, macronutrients, and micronutrients as well as the contribution of each of the macronutrient to energy content. Misreporting of energy intake will be identified using the Goldberg criteria [50], and sensitivity analysis will be undertaken to assess their inclusion or exclusion from the primary analysis. Energy and nutrient intakes will be compared with Australian Nutrient Reference Values [51] applicable for each age and sex group and the usual intakes from the latest Australian Health Survey [6]. Multivariate regression models will be used to determine the various health, social, and environmental factors associated with consumption of energy and nutrients. To control for multiple comparisons, a significance level of *P*<.01 will be considered for these calculations.

Demographics questionnaire.Anthropometry and diet statusSelf-reported height and weightHow often the participant attempted weight loss in past 12 months, including currentlyWhether the participant is motivated by eating healthy food, losing weight, staying fit and active, or their appearanceDiet and eating behaviorsSelf-perceived healthiness of their dietFood avoidance for health, cultural, or ethical reasons, including vegetarianismSupplement useFrequency and usual timing of meals and snacksFood securityAdequacy of factors influencing diet, including cooking skills, cooking equipment, time available to cook, and access to healthy foods in their local areaQuality and variety of healthy foods in their local areaWho does the cooking in their householdHow often meals and snacks are eaten in front of the televisionAverage weekly amount they spend on eating out of homeReasons for eating out of homeNutrition literacyKnowledge of the Australian Government’s recommended number of serves of the 5 core food groupsHealth behaviorsAlcohol consumption and consumption patternsPhysical activity and sedentary behaviors at work and during leisure timeSleep patterns and durationSelf-perceived health and well-beingTobacco and e-cigarette useDietary monitoringWhether they would be interested in logging single foods with appsWhat aspects of their diet would participants be interested in logging (if any)Eat and Track app usabilityEase of useIf the app is frustrating to useWhether the participant had to make corrections

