### Conclusions

This study is the first in Australia to provide detailed information on foods purchased and eaten out of home. By incorporating information from the largest fast food chains in Australia in the app’s food composition database, it is also the first dietary assessment app internationally to have a specific focus on eating out. The requirement of participants to record where they sourced each food or drink will also provide the first estimation of how often young Australians are eating out, and what proportion of their nutritional intake is derived from such meal occasions. This will enable the identification of foods and consumption behaviors of concern that should become the focus of future health promotion efforts for this target audience. Accurate and detailed measurement is important to ensure evidence-based programs.

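### Even quotas with no stated weighting: overall estimates for young Australians may describe the quota mix, and the ±3% margin allows nothing for weighting

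*Protocol article*

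**What the plan says.** **Sampling.** Under Population Sampling, the protocol article states: "Purposive sampling will be conducted to ensure quotas for different demographics are captured". It asks for equal numbers of males and females and then states: "The sample will be constituted to ensure an even distribution of participants in the older age bracket (25 to 30 years"). The same sentence extends the even split to the younger bracket, to metropolitan versus regional areas (major cities versus everywhere else) and to lower versus higher SES areas (deciles 1-5 versus 6-10). Recruitment is through a fundraising event, newsletters, noticeboards and social media, and the Recruitment section adds: "Snowball sampling will also be utilized".

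**Precision.** The size is given as follows: "A total of 1008 participants will be recruited to the study". The article attaches this precision claim to that number: "which provides a margin of error of ±3% on all estimates of proportions (with 95% CI").

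**Analysis.** For intakes, the first subsection of the Statistical Analysis section says: "Data collected from the EaT app will be used to determine mean, median, and 95% CI of daily intakes of energy". The results are also to be set against usual intakes from the national health survey. The next two subsections plan mean food-group intakes, the share of participants meeting recommended serves, and the average frequency of eating out. None mentions weights, post-stratification or standardisation, and none says that the estimates will be unweighted.

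**Target.** Knowledge Gaps says that the data will be collected "in a population sample of 18- to 30-year-old Australians". The Conclusions promise the "first estimation of how often young Australians are eating out".

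**The concern.** An even split is a sensible allocation for comparing subgroups. It suits an overall estimate only if the population is also split evenly, or if the strata are put back into their population proportions. Without one of these, any difference between strata enters the overall figure as bias, and more participants recruited under the same quotas would not reduce it.

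Two outputs are exposed: the headline figures on how much and how often young adults eat away from home, and the comparison with the national survey. A gap from the survey could come partly from the quota mix and be read as a real difference in diet.

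The precision statement is tied to the same question. It covers all estimates of proportions, yet it is the figure for an equally weighted simple random sample. If totals are weighted, it is too narrow. If they are not, the interval is centred on the quota mix. Both worries vanish only where the population split is close to 50:50, which the article does not show.

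**Working it through.** **Inputs from the protocol article (Population Sampling):** n = 1008; sample share 0.5 in each half of every quota; 95% confidence; stated margin ±3%.

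**Assumptions, not in the document:** a metropolitan share W of NSW 18- to 30-year-olds of 0.65 to 0.80, and an illustrative metropolitan-regional difference d of 10 percentage points in some proportion.

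**Step 1: reproduce the stated margin.** With p = 0.5 and equal weights, the standard error is √(0.25/1008) = 1.575 points, and 1.96 × 1.575 = 3.09%, which rounds to ±3%. The figure therefore contains no design effect.

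**Step 2: bias of the unweighted overall proportion.** The sample gives 0.5·p_metro + 0.5·p_regional, and the population value is W·p_metro + (1 − W)·p_regional. The absolute difference is (W − 0.5) × |d|.

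**Step 3: cost of weighting on area alone.** Design effect = W²/0.5 + (1 − W)²/0.5; margin = 3.09% × √(design effect).

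| Metropolitan share (assumed) | Bias per 10-point difference | Design effect | Effective n | Weighted margin |
|---|---|---|---|---|
| 0.65 | 1.5 points | 1.09 | 925 | ±3.22% |
| 0.70 | 2.0 points | 1.16 | 869 | ±3.32% |
| 0.75 | 2.5 points | 1.25 | 806 | ±3.45% |
| 0.80 | 3.0 points | 1.36 | 741 | ±3.60% |
| 0.50 (even) | 0 | 1.00 | 1008 | ±3.09% |

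Bias scales with d: a 5-point difference halves the second column.

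**Step 4: when weighting pays.** The design effect can be written 1 + 4(W − 0.5)². Weighting adds 4(W − 0.5)² × SE² to the variance and removes (W − 0.5)² × d² of squared bias. It has the lower mean squared error when |d| exceeds 2 × SE = 2 × 1.575 = 3.15 points, for any W other than 0.5. This takes p near 0.5 and treats bias from the area mix as the only bias.

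**Step 5: the other quotas.** The age bands cover 7 and 6 single years. If the years are equally populated, the design effect is [(7/13)² + (6/13)²]/0.5 = 1.006, which is negligible. SES is cut at the decile midpoint, and nothing in the article suggests that an even gender split is far from the population. If SES did depart, the cost would rise: with 75% metropolitan and 40% low SES, taken as independent, the design effect is 1.25 × 1.04 = 1.30 and the margin ±3.52%.

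**The case against.** The strongest reply is that a lack of weighting is inferred from silence. A weighted mean is still reported as a mean, and a journal article may leave weighting to a fuller plan. That stands in part: a reader might infer that the plan prescribes unweighted totals, but the article says neither that nor the opposite. The reply does not rescue the precision statement, because ±3% leaves no room for weights wherever they might be specified.

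Second, regional oversampling depends on a population share that the article does not give. This also stands, so the size is conditional on the assumed range, and 3.0 points is its upper end. A reader might go on to infer that all four quotas distort the totals. The document does not support that: no imbalance on gender, age or SES is shown.

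Third, a reader might infer that area and SES were made quotas because eating out differs by them. The article gives no such reason. Its Background ties rural residence and lower SES to obesity risk, not to eating out. The 10-point difference is therefore an illustration.

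Fourth, census weights cannot turn this into a probability sample. Recruitment is purposive and partly snowball, confined to NSW and limited to people who buy food away from home at least weekly, so there are no known selection probabilities to support design-based intervals. That is correct, and it limits what the fix can claim.

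Finally, much of the plan is untouched. Results within area or SES strata do not depend on the allocation between strata, and the Nutrient Reference Values comparison is already made by age and sex group.

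**Conclusion.** The point holds in a bounded form. The article combines even quotas, overall estimates with no weighting step, a national-survey comparison and population wording, together with a margin that is right only for equal weights. Either the overall figures describe the quota mix or the stated margin is too narrow, unless the population split is near 50:50.

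Under an assumed metropolitan share of 65-80%, the unweighted overall proportion is off by 1.5-3.0 points per 10-point metropolitan-regional difference. The upper end is about as large as the margin itself. Weighting on area alone gives about ±3.2-3.6% in place of ±3.09%.

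This affects overall totals and the national comparison, not the subgroup results. It should be put right before those totals are reported, but it does not undermine the study.

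**What to change.** For the overall estimates and the national-survey comparison:

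- Post-stratify or rake to population counts of NSW residents aged 18-30 on the quota variables: mainly area, with SES, age and gender.
- Use robust or replicate-based variances, and describe the intervals as model-dependent, not design-based.
- Report unweighted overall results alongside, and keep unweighted results within strata.
- Restate the overall margin as about ±3.2-3.6% under the assumed area shares, and recompute it once actual shares are used. It widens further if SES also departs from an even split.
- In Knowledge Gaps and the Conclusions, limit the population wording to NSW young adults who meet the eligibility criteria, including buying food away from home at least weekly.

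The cost is small. Age, gender and home postcode are collected at screening, so the strata can be derived without new data or any change to recruitment; only external population counts are needed. The downside is a slightly wider margin. Weighting also leaves volunteer and snowball selection bias in place, and it cannot correct for eligibility rates that differ between cells, because the counts cover all residents and not only the eligible.

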### Recruitment

Participants will be recruited using a range of methods. The study is being conducted in partnership with Cancer Council NSW, a large nongovernment organization that leads a variety of public health research, health promotion, and fundraising activities. Cancer Council NSW has both a head office and a regional structure that allows recruitment across a diverse selection of ARIA+ and IRSAD codes across the state.

One recruitment method will be to recruit through Relay For Life, a community-driven fundraising event, where teams walk or run laps of a running track for 12 to 24 hours [31]. The Relay For Life events are held in both urban and regional centers, and attract approximately 134,000 participants from a broad cross-section of community in Australia annually [32]. During the event, there are other activities and information stands for participants and spectators, where participants will be recruited.

Additional recruitment will be conducted through electronic newsletters, noticeboards, and social media via Cancer Council NSW and The University of Sydney organizational channels. Snowball sampling will also be utilized, with participants encouraged to forward the study details to their own contacts. The recruitment and participation process is summarized in Figure 1.

**Figure 1 figure1:**
[figure not shown]
Recruitment and participation flowchart.

### Screening and Consent

The screening survey (Textbox 1) will be administered at recruitment to collect basic demographic data and consent using the Web-based REDCap research management system [33]. The REDCap system will be programmed to screen participant demographics to fill the study’s demographic quotas. The REDCap system also allows stratified randomization in the substudy (refer to section below).

After completion of the screening questionnaire and enrollment, participants will be notified of their dietary data collection dates, and emailed instructions on how to download and sign up to use the Eat and Track (EaT) app, and obtain a user guide for the EaT app and a copy of the Australian Bureau of Statistics Food Model booklet [34] to assist with estimating portion sizes. Links to useful information on the study website will also be available, including an electronic version of the Food Model booklet.

The study website (Figure 2) was developed to provide information for those participating in this study and future participants. It contains information about the study, its funding and partners, links to the screening questionnaire, technical guides and videos for participants, and links to the Food Model booklet. Potential participants can also contact the study team via email through the website.

Participants will be taught how to use the app using instructional videos and will have access to these videos at all times throughout the study via the study website. Additionally, participants will need to view 3 tutorial screens in the app before they can start recording their intake. They will then record all food and drinks for 3 consecutive days.

Screening questionnaire.Demographics:AgeGenderAboriginality and ethnicityLanguage spoken at homeEducation attainmentPostal code of home addressLiving arrangementRelationship statusEmployment and studyIncomeScreening questions:Do you own a working smartphone?On average, do you have at least one drink, snack or meal you buy away from home each week?(Females only) To your knowledge, are you pregnant and/or breastfeeding?Have you ever been diagnosed or treated for (choose all that apply)?Anorexia Nervosa (screen out)Bulimia Nervosa (screen out)Other eating disorder (screen out)Mental illnessIllicit drug useDiabetesNone of these

**Figure 2 figure2:**
[figure not shown]
MYMeals Study website.

### The Eat and Track Dietary Intake App

Data will be collected using a customized smartphone app, EaT. The EaT app is an updated version of the research team’s validated app called electronic Dietary Intake Assessment (eDIA) that uses Australian food composition data [35,36]. The EaT app has an improved user interface and underwent iterative development with usability testing using techniques such as the “Think Aloud” protocol [37]. The EaT app allows participants to record what they eat and drink in real time. Underpinning the EaT app is a customized database containing more than 6200 foods and beverages, including 4046 foods and beverages from the Australian Bureau of Statistics’ AUSNUT 2011-2013 database [38] and 2229 fast food menu items sourced from the routinely collected Cancer Council NSW-The George Institute fast food database [39,40]. The EaT app interface supports food searches for many common and commercial brand names to improve the participants’ ability to correctly search and identify foods. In addition, for common foods, the interface presents keywords to speed up searches. For example, when a user types “milk,” a shortlist of all milk types will appear (Figure 2). Previously added foods remain in a shortlist and create a shortcut in the logging screen. The EaT app also supports freeform text entry of foods so that participants can record what they eat if they are unable to locate it in the database.

Once participants have recorded the foods and drinks they consumed, they then enter the amounts ingested into the EaT app (Figure 3), together with the location from which the food was sourced (Textbox 2). Participants were instructed to choose “home” for all foods not purchased and consumed outside the home. While not mandatory, participants are encouraged to weigh and measure the foods and drinks before consumption, and there is a check button to indicate if foods have been weighed. If not weighed, participants are encouraged to use the Food Model booklet to estimate their amounts in household measures, or they can enter a default portion size. These default sizes are based on typically consumed portion sizes for males and females aged 18 to 30 years based on the latest national dietary survey [41]. If participants cannot find a food listed in the app’s database, they will be able to manually enter it as a new food, and this will be flagged to the research team for follow-up. Each entry is time and date stamped, and thereby indicates whether all entries are made at one time or recorded prospectively throughout the day.

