**Objectives:**

The objective of this study was to determine the relative contributions of different food outlets (eg, fast food chain, independent takeaway food store, coffee shop, etc) to the overall food and beverage intake of young adults; to assess the extent to which food and beverages consumed away from home contribute to young adults’ total energy and deleterious nutrient intakes; and to study social and physical environmental interactions with consumption patterns of young adults.

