**Methods:**

A cross-sectional study of 1008 young adults will be conducted. Individuals are eligible to participate if they: (1) are aged between 18 and 30 years; (2) reside in New South Wales, Australia; (3) own or have access to a smartphone; (4) are English-literate; and (5) consume at least one meal, snack, or drink purchased outside the home per week. An even spread of gender, age groups (18 to 24 years and 25 to 30 years), metropolitan or regional geographical areas, and high and low socioeconomic status areas will be included. Participants will record all food and drink consumed over 3 consecutive days, together with location purchased and consumed in our customized smartphone app named Eat and Track (EaT). Participants will then complete an extensive demographics questionnaire. Mean intakes of energy, nutrients, and food groups will be calculated along with the relative contribution of foods purchased and eaten away from home. A subsample of 19.84% (200/1008) of the participants will complete three 24-hour recall interviews to compare with the data collected using EaT. Data mining techniques such as clustering, decision trees, neural networks, and support vector machines will be used to build predictive models and identify important patterns.

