**Figure 3 figure3:**
[figure not shown]
Eat and Track (EaT) app screenshots showing the landing screen, food logging screen, and pink button filtering of foods.

Locations for food source included in the Eat and Track App.Fast food chain (Chain outlets selling takeaway foods, such as burgers, pizza, or fried chicken)McDonald’s, KFC, Pizza Hut, Mad MexCoffee chain (Chain outlets selling predominantly coffee and tea)Gloria Jean’s Coffee, StarbucksCold drink chain (Chain outlets selling predominantly cold drinks, including juice, smoothies, or iced tea)Boost Juice, EasyWay TeaIce creamery/frozen yogurt (Chain or independent outlets selling predominantly ice cream, gelato, or frozen yogurt)New Zealand Natural, Yogurberry, local ice creameryOther takeaway (Independent outlets selling any type of takeaway foods)Local fish and chip shop, local pizzeriaIndependent café or restaurant (Independent sit-down café or restaurant selling any type of cuisine; may also do takeaway food)Asian/Indian restaurant, local café, other restaurantsBakery or patisserie (Chain or independent outlets selling predominantly baked goods, such as cakes, breads, and sweets)Michel’s Patisserie, Muffin Break, local bakeryService station/convenience store (Food bought from service stations or convenience stores, including cafes in these locations)7-Eleven, Wild Bean Café, or BP, Shell or Mobil service stationsPub or club (Restaurants, bars, cafes or bistros in pubs or clubs)Bowling, RSL, sports or community clubs, local hotelsHome (Any food not sourced from the locations above.)Includes homemade food, food prepared by friends or relatives, or foods purchased from supermarkets

At the conclusion of each day’s recording, participants will complete a short survey. This survey will determine whether the day’s food and beverage intake, frequency of eating away from home, physical activity, stress, and sleep levels were higher or lower than usual. Additionally, self-reported healthiness of the day’s dietary intake, assessed by a 5-point Likert scale, ranging from “very unhealthy” to “very healthy” was included in the end of day survey.

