### Data Mining

In addition to our usual epidemiological approach, the data will be analyzed using data mining and machine learning techniques employed by information technology scientists. A clustering technique to automatically partition the participant population into groups with similar energy and nutrient intake, and food group consumption patterns will be applied. The resulting clusters of food consumption will be labeled according to their common patterns, for example, high processed meat and takeaway consumption; high fish, fruit, and vegetable consumption. These clusters will then be analyzed for the predominant health, social, and environmental characteristics of each cluster and checked for common associations (such as participants with healthier diets, also exercising regularly, having healthier BMI, not skipping breakfast, and mainly eating at home).

Data mining techniques such as decision trees, neural networks, and support vector machines will be used to build predictive models; for example, to predict the type of diet (high quality or poor quality, assessed by the Healthy Eating Index for Australian adults [53]) based on the frequency and contribution of foods eaten away from home and health, social, and environmental variables. In contrast to standard statistical methods such as multivariable linear regression, these techniques are capable of assessing complex nonlinear relationships and are less sensitive to outliers (data points that correspond to exceptional, nonrepresentative cases). Decision trees offer additional advantage in that they can be represented as a set of if-then rules and are thus easy to explain and use for decision making.

Association rule and time-series mining will be used to find frequent relationships between the variables, for example, what types of foods are typically eaten together at home and away from home by the different groups, whether budget constraints and high stress levels imply fast food consumption regardless of the education level, and whether there are temporal associations.

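### The text describes one food-source field with two conflicting rules for its *Home* code, and under either rule at least one stated outcome is misclassified

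*Protocol article*

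**What the plan says.** **What is recorded.** The abstract (Methods) promises two locations: "Participants will record all food and drink consumed over 3 consecutive days, together with location purchased and consumed in our customized smartphone app". The section The Eat and Track Dietary Intake App describes one: "they then enter the amounts ingested into the EaT app (Figure 3), together with the location from which the food was sourced (Textbox 2"). Textbox 2 is titled as a list of food-source locations and has nine outlet types plus *Home*. Knowledge Gaps names only the place of purchase, and the Conclusions speak of "The requirement of participants to record where they sourced each food or drink". No part of the body describes a field for where an item was eaten.

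**How *Home* is coded.** The app section says participants were told to choose it "for all foods not purchased and consumed outside the home". Textbox 2 defines it as anything not sourced from a listed outlet, and adds: "Includes homemade food, food prepared by friends or relatives, or foods purchased from supermarkets".

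**What is to be estimated.** The abstract's objectives and the Aims ask for two things. One is the contribution of each outlet type to overall intake. The other is, in the abstract's words, "to assess the extent to which food and beverages consumed away from home contribute to young adults’ total energy and deleterious nutrient intakes". The analysis section on foods purchased and eaten away from home takes the joint condition, bought and eaten away, as its outcome. Data Mining gives as an example "what types of foods are typically eaten together at home and away from home by the different groups".

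**The concern.** Three outcomes are in play and each needs different information. Outlet contribution needs the source of the food. Food bought and eaten away needs the source and the place of eating. Food consumed away needs the place of eating, whatever the source. A single location field cannot carry all three, and the two rules for *Home* treat takeaway eaten at home in opposite ways.

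At stake is the meaning of the headline result, the share of energy and nutrients attributed to eating away from home. The coding rule decides whether takeaway eaten at home counts towards it. Participants may have met both rules, so the data may also mix the two. Such misclassification does not shrink with more participants.

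**Working it through.** The article states no figure on this point, so there is none to reproduce. The check sets the two coding rules against the three outcomes.

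**Step 1. How each kind of item is coded.** The instruction is read as requiring both purchase and consumption outside the home for a non-*Home* code.

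| Item | Under the instruction | Under Textbox 2 |
|---|---|---|
| Outlet food eaten out | outlet | outlet |
| Outlet food eaten at home | *Home* | outlet |
| Homemade or supermarket food eaten at home | *Home* | *Home* |
| Homemade or supermarket food eaten elsewhere | *Home* | *Home* |

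The rules differ only in the second row. In the last row the list offers no code other than *Home*, even for supermarket food bought and eaten while out.

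**Step 2. True and coded shares.** Let S be the share of energy sourced from outlets, f the fraction of that energy eaten at home, and g the fraction of the remaining energy eaten elsewhere.

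- Outlet contribution: S
- Bought and eaten away: S(1 − f)
- Consumed away: S(1 − f) + (1 − S)g
- Coded non-*Home* under the instruction: S(1 − f)
- Coded non-*Home* under Textbox 2: S

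**Step 3. Error, coded minus true.**

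| Outcome | Instruction | Textbox 2 |
|---|---|---|
| Outlet contribution | −Sf | 0 |
| Bought and eaten away | 0 | +Sf |
| Consumed away | −(1 − S)g | Sf − (1 − S)g |

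Neither column is zero throughout. The same algebra applies to each outlet type with its own S and f, so the error may differ between outlets. If some participants follow one rule and some the other, the coded share lies between S(1 − f) and S.

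**Step 4. Illustration on assumed values.** The documents give none of S, f or g. Take S = 30%, f from 0 to 50% and g from 0 to 20%.

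- Sf runs from 0 to 0.30 × 0.50 = 15 points.
- (1 − S)g runs from 0 to 0.70 × 0.20 = 14 points.
- Bought and eaten away runs from 30% down to 0.30 × 0.50 = 15%.
- Consumed away runs from 15% (f = 50%, g = 0) to 0.30 + 0.14 = 44% (f = 0, g = 20%).
- Textbox 2 coding reports 30% in every case.

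Over the same f and g, consumed away runs from 10% to 36% when S = 20%, and from 20% to 52% when S = 40%. These ranges show only that the definitions can diverge. They do not estimate the error in this study.

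**Step 5. Could another instrument fill the gap?** The final questionnaire asks for self-reported frequency of, and spending on, food bought and eaten away over the 3 days. The end-of-day survey asks whether eating away was more or less frequent than usual. Both are person-level or day-level answers and give no energy or nutrient share.

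**The case against.** The strongest reply is that the instruction already brings place of eating into the code. If it governs, every non-*Home* entry is food both bought and eaten outside the home, which is exactly the outcome in the analysis section. That stands, and Step 3 shows zero error there. A reader might infer from the single field that the away-from-home outcomes cannot be scored at all; the documents do not support that. The same rule, however, takes takeaway eaten at home out of the outlet contributions, which are also a stated objective.

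A second reply is that the place of eating may in fact be collected. The abstract says so, the app screenshots are not available here, and an article condenses. This also stands in part: the text describes no such field but does not exclude one, so it cannot be concluded that the information is missing beyond repair. It does not remove the inconsistency, because the article itself describes the field, prints its categories and departs from its own abstract.

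A third reply is that the article uses prepared, purchased, consumed and eaten away from home loosely for one construct that is mainly about source. That is plausible, and it is why a change of wording is enough. The Data Mining example is illustrative and carries little weight alone.

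**Conclusion.** The point holds as an inconsistency in what is recorded and how it is coded. The abstract's two locations do not match the single source field in the body, and the two definitions of *Home* conflict. Under the instruction, outlet contributions are understated. Under Textbox 2, food bought and eaten away is overstated. Under either rule, food consumed away cannot be derived item by item as described.

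The direction of the first two errors follows from the coding rules whenever some outlet food is eaten at home. For food consumed away, the instruction can only understate, while Textbox 2 can err either way. The size cannot be computed from the documents.

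A reader might set an assumed error of several points against the ±3% margin in Population Sampling and call it a multiple of that margin. This is not supported: the inputs are assumed, and the margin describes sampling error in estimated proportions, not misclassification of an energy share.

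The conclusion rests on two assumptions: that the instruction means both purchase and consumption, and that the app has no undescribed place-of-eating field.

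**What to change.** 1. Reconcile the abstract, the participant instruction and Textbox 2 to one source-based rule, under which outlet food keeps its outlet code wherever it is eaten.
2. Correct the abstract's Methods to say that the app records the location of purchase.
3. Restate the outcomes in the abstract's objectives, the Aims, the analysis section on food bought and eaten away, and Data Mining as food sourced from outlets, wherever eaten.
4. If the app does hold a place-of-eating field, describe it in the app section and cross it with source in that analysis. The outcomes defined by place of eating can then be kept.
5. Flag records already entered under the existing instruction. In a sensitivity analysis, treat takeaway eaten at home as possibly coded *Home*. One practical marker is a *Home*-coded entry chosen from the 2229 fast food menu items in the app database, although this reaches only foods on that list.

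Steps 1 to 3 cost a wording change, a revised participant instruction and a narrower claim: the study would report food sourced from outlets and not food eaten away from home. Step 5 costs one extra analysis, and early records will remain uncertain for takeaway foods outside the menu database.
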